**Figure 1 F1:**
[figure not shown]
Study diagram (MDT, multidisciplinary team; CPET, cardiopulmonary exercise testing).

## Intervention

### Prehabilitation programme

In addition to psychological and nutritional support, which is a standard part of cancer treatment, the foundation of the prehabilitation programme is physical training. The nutritional support of probands enrolled in the study is similar to that of other cancer patients. Every patient is screened and assessed by a dietitian for potential nutritional supplementation as part of the standard care. This is followed by tailored dietetic advice regarding food, protein, energy intake, and supplementation. In some cases, patients may require enteral or parenteral feeding, which is occasionally administered through adjuncts such as nasoenteric tubes, feeding jejunostomies, or, in rare instances, total parenteral nutrition.

Even before starting neoadjuvant therapy, during the first clinical examination, the patient will be thoroughly educated about the prehabilitation programme, and they will be given an exercise diary to record their daily physical activity.

The initial examination will include an assessment of the overall condition, including obtaining past medical history and testing grip strength. Validated InBody230 body composition analyser (Biospace Co., LTD., Coalville, United Kingdom), which fulfils the standards of IEC60601-1(EN60601-1), will be used to analyse body composition (percentage of water, fat, muscle mass). Patients will be educated on the use of technologies that will record monitored parameters (steps, heart rate, weight), and they will be given a telemetry set—a MiBand 5 pedometer (Xiaomi Inc, Beijing, China), a Galaxy A13 mobile phone (Samsung Electronics, Suwon, South Korea), a W62 telemetry scale (Zhongshan Loease Electronic Technology Co, Ltd, Zhongshan, China), and an initial CPET will be performed.

For one week, the patient's physical activity will be monitored telemetrically by recording the number of steps. Based on this, a baseline value will be established, from which the subsequent exercise dosage will be derived.

### Physical training

Physical training will consist of endurance (walking) and strength components. Walking is the most natural physical activity for humans. The training programme aims to be individualised by the research team. The basis for determining the number of steps per day is the baseline value for each patient. This will be increased by 10%–15% every week until the date of surgery. If the increase is not tolerated by the patient, the last increased step count will be retained, and consideration of further increase will be postponed until the following week. The expected total increase in steps is 120%–180% of the baseline. The authors are aware that not every patient can achieve these values. Within the feasibility study, the authors want to verify the acceptable dosing of the load. At the same time, authors' goal is for the patient to perceive their load at medium intensity (measured by the Borg scale, corresponding to 3–4 out of 10) for 30 min per day.

Strength training will be applied using exercises to strengthen the upper (biceps and triceps groups through exercises without and with dumbbels or rubber expander, wall push ups) and lower limbs (strengthening of gluteal, quadriceps, hamstrings and culf muscles through squats with or without back support, standing up from a chair, toe raises, leg raises) and the core. Training will involve a set of eight exercises in several difficulty variations. The patient chooses a variant that he or she can perform and gradually can choose a more difficult variant of the exercise. Each exercise will be done for one minute. The set will be repeated twice. The total strength training time will take approximately 20 min. The patient will perform this set seven days a week. Achievement of Borg 3–4 for strength training is not required. A description of each exercise and photo documentation is part of the exercise diary. The patient is also taught about possible mistakes when performing each exercise and the mistakes are photo documented. The education in the training program is part of the first clinical examination.

If interested, the patient can undertake additional activities (running, cycling, etc.) during the study. Patients will be encouraged to do these activities, and these will be recorded.

Patients will record their daily physical activity in their exercise diaries (number of steps per day, strength training, subjective perception of intensity according to Borg, other physical activities).

Physical training will be carried out throughout the neoadjuvant therapy and will continue after its completion, up to 1–2 weeks before surgery.

### Data monitoring

Data collection will be obtained in two ways: by contacting patients by phone and by remote monitoring. During physical training, the patient will be contacted by phone once a week by the study researcher to support them, monitor data from the exercise diary (number of steps per day/week, number of days per week performing strength exercises, subjective perception of intensity according to the Borg scale during aerobic activites, other physical activities from the previous week). During the conversation, any patient difficulties and problems will be discussed. The patient will have the opportunity to participate in specifying the physical load (number of steps) for the following week.

Remote monitoring will be ensured in collaboration with the telemedicine services centre. Patients will be equipped with the aforementioned telemetry set to ensure data capture. Data will be transmitted continuously to the research team and evaluated once a week before a phone call with the patient.

The telemedicine service centre also includes a control centre, which will monitor threshold and critical values, track trends of measured values, identify and display incidents (alerts and alarms), generate reports, secure store and archive data, transfer data from client terminals to the monitoring centre, and provide technical support to system users.

### Termination of the prehabilitation programme

The exercise programme will be terminated 1–2 weeks before the scheduled surgical procedure. During this period, a control CPET will be carried out, a control examination of the grip strength of the dominant hand, a control questionnaire of the quality of life, and the patient's weight will be measured. During the postoperative period (within 1–2 weeks after surgery depending on his current state of health) a questionnaire survey of the patient's subjective perception of the exercise programme will be conducted.

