## Methods

This is a feasibility study focused on patients with oesophagogastric cancer or rectal cancer who were, based on the decision of the multidisciplinary team (MDT) of the University Hospital in Ostrava (FNO), indicated for neoadjuvant therapy in the preoperative period.

These groups of patients were chosen as they are commonly treated with neoadjuvant treatment, which opens a time window for the application of a prehabilitation programme. The prehabilitation programme is designed in the form of physical training aimed at improving or retaining cardiorespiratory fitness as well as the strength of selected muscle groups. Each patient also receives nutritional support. The programme is designed to minimise significant time demands on medical staff, so it will be implemented in the patient's home environment. The study aims to answer question whether the selected patients will be able to complete a home exercise regimen during the preoperative period when they undergo neoadjuvant therapy.

The primary outcomes to evaluate the feasibility of the study are:
1.Percentage of patients who consent to participate in the study out of all diagnosed and for neoadjuvant therapy indicated patients in the monitored period. The reasons for refusing to participate will be recorded.2.The percentage of patients who consent to participate in the study and who remain participants until the end of the study period, out of all consented patients.3.Individual patient compliance—defined as the number of days the patient wore a smart bracelet, carried out or attempted to complete the prescribed exercise programme (aerobic exercise and strength training), and remained accessible for follow-up telephone contact, out of the total number of days in the observed period.4.All adverse events related to the prehabilitation programme implementation.

Secondary outcomes include changes in physical fitness parameters obtained from cardiopulmonary exercise testing CPET—peak oxygen uptake, anaerobic threshold test performed on a Bicycle ergometer ERGOSELECT 5 (Ergoline GmbH, Bitz, Germany and COSMED srl, Rome, Italy) using a ramp protocol with a gradual increase in load of 0.5 W per kilo per min, changes in grip strength measured by hand dynamometer, changes in body composition, Borg's scale of perceived exertion, changes in health-related quality of life measured by EORTC QLQ-C30 quality of life questionnaire, and a subjective perception of the exercise programme.

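### Change in body composition is a secondary outcome, but the end-of-programme assessments schedule no second body composition measurement

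*Protocol article*

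**What the plan says.** Four parts of the protocol article bear on this.

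- **Outcome.** The Abstract and the Methods section both list body composition as a secondary outcome, worded as a change. In Methods it stands in the run "changes in grip strength measured by hand dynamometer, changes in body composition, Borg's scale of perceived exertion".
- **Baseline.** Under Prehabilitation programme, the InBody230 analyser "will be used to analyse body composition (percentage of water, fat, muscle mass") at the initial examination. The same section limits the telemetry to "technologies that will record monitored parameters (steps, heart rate, weight").
- **End of programme.** Under Termination of the prehabilitation programme: "During this period, a control CPET will be carried out, a control examination of the grip strength of the dominant hand", followed by "a control questionnaire of the quality of life, and the patient's weight will be measured". The window is 1–2 weeks before surgery. The only later contact described is the postoperative questionnaire on how the patient perceived the programme.
- **Analysis.** Statistical methods names four metric variables for the paired tests: peak oxygen uptake, anaerobic threshold, number of steps and grip strength. Body composition is not among them. The Abstract says that secondary outcomes will be compared between the two diagnostic groups.

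**The concern.** A change needs the same quantity measured twice. Here the first measurement is specified by device and by component, while the assessment that should supply the second names body weight instead. Staff who follow the termination section would weigh the patient and not repeat the analyser measurement.

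The gap cannot be repaired later. The control assessment is the last one before surgery, and a pre-surgical value that was not taken cannot be obtained afterwards. The article offers its results as groundwork for larger controlled studies, and those studies would have no estimate of this change or of its variability. The Introduction cites retained muscle mass among the benefits seen in an earlier randomised trial of prehabilitation, so the outcome is relevant to the rationale.

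**Working it through.** No sample size, power or error rate is involved. The check is a comparison of the assessment lists.

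**Step 1. Is each physical measure available at both ends, as the text is written?**

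| Measure | Start (Prehabilitation programme) | End (Termination, or monitoring) | Change computable? | Named for paired test? |
|---|---|---|---|---|
| CPET: peak oxygen uptake, anaerobic threshold | initial CPET | control CPET | yes | yes |
| Grip strength | initial examination | control examination, dominant hand | yes | yes |
| Steps | one-week baseline | telemetry and diary | yes | yes |
| Body weight | telemetry scale | weighed at the control assessment | yes | no |
| Body composition: water, fat, muscle % | InBody230 | none listed | **no** | no |

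Only the last row lacks a second value.

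**Step 2. Could another source supply it?** Data monitoring describes a weekly call and diary review covering steps, strength-training days, Borg rating and other activities. It also describes the telemetry stream, whose monitored parameters are steps, heart rate and weight. Neither includes body composition.

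**Step 3. Could weight stand in?** Let W be weight and f the fat fraction, with 0 for baseline and 1 for the end.

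- The outcome for fat percentage is f1 − f0.
- The text supplies W0, W1 and f0.
- Fat mass at the end is W1 × f1, and f1 is not measured. Any f1 is compatible with the same W0, W1 and f0, so f1 − f0 is undetermined.
- The same holds for the water and muscle fractions.

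**Step 4. What follows for the analysis?** With no f1 there are no pairs for a within-patient test. The between-group comparison could use only baseline values, which describe the two groups before the programme and not their change.

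**Step 5. How much of the study is affected?** Methods lists six secondary items: CPET parameters, grip strength, body composition, Borg rating, quality of life and subjective perception. Four of these are worded as changes, and one of those four has no second measurement scheduled. None of the four primary outcomes (consent, retention, compliance, adverse events) uses body composition.

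**The case against.** The strongest reply is that this is a condensed article. The termination section does not call its list complete, Figure 1 is not visible, and the full protocol may schedule the repeat. That is fair, and it rules out saying that the outcome will be lost. It does not remove the inconsistency. The article gives an itemised list at each end. The second repeats the clinic tests of CPET and grip strength but names weight where body composition would be expected. If Figure 1 lists the repeat, the termination section still disagrees with it.

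A second reply is that little depends on this outcome. The stated aim of the training is cardiorespiratory fitness and muscle strength. CPET addresses the first and grip strength bears on the second; both are measured at each end and named for paired testing. That stands. It limits the severity, and it means one should not argue that preserving muscle mass is the programme's declared target.

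A reader might draw three stronger inferences that the text does not support.

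- **That quality of life has no baseline either.** The initial examination is described as an "assessment of the overall condition, including obtaining past medical history and testing grip strength", followed by the analyser, the telemetry set and CPET, with no questionnaire listed. But the outcome is "changes in health-related quality of life measured by EORTC QLQ-C30 quality of life questionnaire", the end questionnaire is called a control in the same sentence as two tests that do have baselines, and a paired Wilcoxon test is planned for questionnaire scores. All three presuppose a baseline questionnaire. This is an unlisted item in a condensed article, not a contradiction.
- **That the home scale cannot measure composition.** The article says which parameters are monitored. It does not say what the scale is capable of.
- **That the end assessment consists only of weighing.** It also covers CPET, grip strength and quality of life; weight is the only *body* measure.

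**Conclusion.** The point holds for body composition. As the text stands, the change in water, fat and muscle percentage, and its comparison between the oesophagogastric and rectal groups, cannot be computed because only the baseline measurement is scheduled. This is a disagreement between the outcome list and the assessment list.

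The conclusion assumes that the termination section is followed as written and that no unseen document, Figure 1 included, adds the repeat. It should be fixed, but it is not critical: one secondary outcome is affected and the feasibility conclusion does not depend on it. It still deserves correction because a missed measurement cannot be recovered after surgery and the correction is cheap.

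**What to change.** Choose one of two routes and make all sections agree.

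1. **Keep the outcome.** Add the same InBody230 measurement, with the same three components, to the control assessments under Termination of the prehabilitation programme. In Statistical methods, add body composition to the metric variables for paired testing.
2. **Drop the repeat.** If no second analysis is intended, restate the outcome in the Abstract and in Methods as change in body weight. State which baseline weight is used, since the baseline text mentions weight only as a telemetry parameter. The InBody230 result then becomes a baseline descriptor.

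Under either route, check Figure 1 against the revised text. Route 1 costs one brief non-invasive measurement per patient, on a device already in use and at a visit already planned. Route 2 costs a change of wording and gives up any information on fat and muscle separately. Route 1 is preferable while patients can still be measured before surgery.

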## Statistical methods

The collected data will be entered into electronic forms. Basic descriptions of individual groups will be made using descriptive statistical methods. Continuous normally distributed variables will be presented as mean and standard deviation, skewed continuous variables and ordinal variables as median and interquartile range. Categorical data will be presented as numbers and percentages. Demographic characteristics will be compared between groups using a *t*-test or a Mann-Whitney U test (age) and a chi-square or Fisher's exact test (gender). Normality of data will be assessed by a Shapiro-Wilk test. Primary outcomes will be reported as numbers and percentages. To determine the significance of changes during the monitored period, for metric data (peak oxygen uptake, anaerobic threshold, number of steps, grip strength), depending on their distribution, a paired *t*-test or a paired Wilcoxon test will be used. The paired Wilcoxon test will also be used for ordinal data (scores from questionnaires). Comparisons between two diagnostic patient groups for continuous data, again depending on the properties of their distribution, will be performed using a two-sample *t*-test or a Mann-Whitney U test, and for ordinal data, a Mann-Whitney U test. *P*-values less than 0.05 will be considered statistically significant. Statistical analyses will be performed using the IBM® SPSS® Statistics version 28 (IBM, Armonk, USA).

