## Abstract

**Aims:**

The concept of prehabilitation, defined as interventions aimed at enhancing a patient's functional capacity prior to an impending physiological stressor, may contribute to reduced postoperative morbidity and mortality. The study's goal is to verify or refute the feasibility of a prehabilitation programme for two diagnostic patient groups during neoadjuvant chemo(radio)therapy, which is prescribed before the scheduled surgical procedure. This is a single group study design, with all patients enrolled receiving the intervention.

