Inclusion criteria for this study are age >18 years and planned resection for locally advanced oesophagogastric adenocarcinoma or adenocarcinoma of rectum with planned neoadjuvant therapy and ability to complete CPET and able to sign informed consent for study participation. Exclusion criteria for this study are contraindications to CPET or inability to perform CPET or daily exercises due to orthopaedic limitations (e.g., amputation, severe gonarthrosis, coxarthrosis) or inoperability determined by the MDT decision or synchronous malignant disease or multivisceral resection or planned non-surgical therapeutic procedures.

The sample size was set at 40 patients given the feasibility nature of the study (34). The patient will be referred to oncologist once MDT agrees on the therapeutic plan. The oncologist, overseeing the oncological treatment, will inform the patient about the possibility of participating in the study and if patient agrees to participate in the study, informed consent will be signed before start of the neoadjuvant therapy.

The length of the prehabilitation programme is based on the length of oncological treatment which for group of patients with oesophagogastric adenocarcinoma consists of four cycles of neoadjuvant chemotherapy at 15-day intervals for a total length of 60 days. The restaging time takes 14–21 days, and time from restaging to surgery usually takes 7–14 days. The total duration for the prehabilitation programme for this group of patients will be about 11 to 13 weeks. For rectal adenocarcinoma, the oncological treatment involves 4–5 weeks of chemo(radio)therapy, followed by restaging after a 3–4 week interval and followed by surgery 1–2 weeks later. The total duration of the programme for this diagnostic group will be around 8 to 11 weeks (Figure 1).

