## Conclusion

The aim of the study is to demonstrate or refute the feasibility of the prehabilitation programme in the form of physical training for two diagnostic patient groups (oesophagogastric adenocarcinoma and rectal adenocarcinoma) during neoadjuvant chemo(radio)therapy, which is indicated before the planned surgical procedure. The study aims to answer the basic research question of whether, during the preoperative period of neoadjuvant therapy, selected patients will be able to complete a home-based exercise regimen.

The study's investigators anticipate that the set prehabilitation exercise programme for patients undergoing neoadjuvant chemo(radio)therapy will be safe and feasible. The results of the study may form the basis for larger, multicentric, controlled studies in the future.

The main limitation of this study is the necessity for coordination between a diverse interdisciplinary team of specialists (oncology, surgical rehabilitation, functional diagnostics, telemetry, nutrition, etc.). Due to the high workload of these specialised outpatient clinics, this may result in a prolonged period before the proband is included in the prehabilitation programme. The extensive range of clinical conditions and physical fitness levels of the probands prior to their inclusion in the study may be the underlying reason for the inability to initiate prehabilitation. Moreover, the rapid advancement of technology in the field of telemedicine may introduce novel forms and applications of telemetry throughout the course of the study.

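### The article promises a verdict for or against feasibility, but no primary outcome has a value that would count against it

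*Protocol article*

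**What the plan says.** The aim is worded as a two-way verdict in two places. The Abstract (Aims) says: "The study's goal is to verify or refute the feasibility of a prehabilitation programme for two diagnostic patient groups". The Conclusion says: "The aim of the study is to demonstrate or refute the feasibility of the prehabilitation programme". The Conclusion adds that the investigators expect the programme to prove safe and feasible.

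The Methods section lists four primary outcomes:
- consent among all indicated patients (uptake);
- staying in the study among those who consented (retention);
- each patient's compliant days over all observed days (compliance);
- adverse events related to the programme.

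None carries a target, a cut-off or an unacceptable level.

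On analysis, the Statistical methods section says: "Primary outcomes will be reported as numbers and percentages". The same section names tests for changes in fitness, steps, grip strength and questionnaire scores and for differences between the diagnostic groups, and sets a 0.05 significance level. The Abstract (Methods) adds that primary as well as secondary outcomes will be compared between the diagnostic groups.

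On size, the Methods section says: "The sample size was set at 40 patients given the feasibility nature of the study", with a citation. The design has no control group: "This is a single group study design, with all patients enrolled receiving the intervention".

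**The concern.** An aim to demonstrate or refute needs some result that would count as refutation. The article states the aim and the primary analysis, and nothing connects them. A retention of 85%, 65% or 45% would each be reported as a percentage, and each could be called feasible or not afterwards. The investigators have also said in print which answer they expect.

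The article presents the results as a possible basis for larger controlled multicentre trials. Planners of such a trial would inherit a verdict reached after the data were seen, resting on point estimates from about 40 patients with no stated uncertainty.

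**Working it through.** **The plan's own figure.** N = 40 can be neither reproduced nor contradicted. The article gives no expected rate, target, precision, significance level or power for any feasibility outcome. The rates and targets below are therefore illustrations.

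**Step 1. Is there a refuting value anywhere?**
- Uptake: a percentage of all indicated patients; no target.
- Retention: a percentage of consented patients; no target.
- Compliance: a ratio of days per patient; no level that makes a patient compliant, and no target share of such patients.
- Related adverse events: all recorded; no unacceptable rate.
- Group comparison: asks whether the two diagnoses differ. Both groups could do equally badly and the comparison would show nothing.
- The 0.05 level: attached to tests of change and group differences, not to feasibility.

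No element of the text turns an observed value into a refutation.

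**Step 2. How uncertain are the percentages?** Exact (Clopper-Pearson) 95% limits for x of n are the 2.5% quantile of Beta(x, n − x + 1) and the 97.5% quantile of Beta(x + 1, n − x).

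| Observed | Percentage | Exact 95% interval |
|---|---|---|
| 28/40 | 70% | 53.5% to 83.4% |
| 32/40 | 80% | 64.4% to 90.9% |
| 16/20 (equal split by diagnosis assumed) | 80% | 56.3% to 94.3% |
| 0/40 related events | 0% | upper limit 1 − 0.025^(1/40) = 8.8% |

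The n = 40 rows suit outcomes whose denominator is the consented patients. They do not apply to uptake, whose denominator is all indicated patients. If 40 of 80 consented, for instance, the interval would be 38.6% to 61.4%.

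**Step 3. Could 40 patients carry a verdict?** Take one rule: feasible if the whole 95% interval lies above the target, not feasible if it lies wholly below, otherwise inconclusive.

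| Illustrative target | Feasible | Inconclusive | Not feasible |
|---|---|---|---|
| 60% | 31/40 or more | 18 to 30 | 17/40 or fewer |
| 70% | 34/40 or more | 22 to 33 | 21/40 or fewer |

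Check at the 60% target: 31/40 gives 61.5% to 89.2%, and 17/40 gives 27.0% to 59.1%. A cut at 30/40 would not fit this rule, because its interval (58.8% to 87.3%) includes 60%.

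Binomial probabilities for the 60% target at n = 40:
- P(X ≥ 31) = 1.6% if the true rate is 60%, and 73% if it is 80%.
- P(X ≤ 17) = 1.9% if the true rate is 60%, and 69% if it is 40%.

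A looser one-sided rule (30 or more) has probability 3.5% at a true 60% and 84% at a true 80%. So 40 patients can separate rates about 20 points apart. Smaller gaps are harder: for 70% against 85%, a cut at 34/40 has power 61%. Within an assumed group of 20, for 60% against 80%, a cut at 17/20 has power 41%.

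**The case against.** **Only a journal article is at hand.** Intervals for proportions, and perhaps progression cut-offs, may stand in a full protocol or analysis plan. This has weight: the absence of intervals is the weaker part of the point and would not carry it alone. It does not dispose of the rest. The article publishes an aim that calls for a criterion and a primary analysis that contains none, and what counts as refutation belongs with the aim.

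**The verbs may be meant loosely.** Elsewhere the article asks descriptively whether patients can complete the regimen, and a formal go/no-go rule is not obligatory in a single-group study of 40. That is fair, and it is why rewording the aim is an acceptable remedy. The expectation of a favourable result is a stated hypothesis and no evidence of bias.

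**Stronger readings that do not hold.** A reader might infer that 40 patients are too few for a verdict. The calculation shows otherwise for the whole sample at gaps of about 20 points. Whether the cited source ties 40 to a precision cannot be checked here. A reader might also infer that percentages are the only use of the primary outcomes. The text does not say so: the Abstract promises a group comparison, and the general rule for continuous variables (mean and SD, or median and IQR) could cover compliance.

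**Conclusion.** The point stands in limited form. The article promises to demonstrate or refute feasibility, states its primary analysis as numbers and percentages, and gives no primary outcome a value that would refute feasibility. The promised group comparison does not fill the gap. As written, the verdict can only be set after the data are seen.

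The size of the ambiguity depends on the target, which has to be assumed. At 60%, any retention from 18 to 30 of 40 is compatible with a true rate on either side; at 70%, any from 22 to 33. The figures assume 40 consented patients as denominator and independent patients. Those by diagnosis also assume a 20/20 split that the article does not state. This should be corrected, but it is no reason to change the design or the sample size.

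**What to change.** **In Statistical methods**, replace the sentence on primary outcomes with text to this effect: *Uptake (denominator: all indicated patients), retention (denominator: consented patients) and the proportion of patients with a programme-related adverse event will be reported with exact 95% confidence intervals, overall and descriptively by diagnosis. Compliance will be reported as the distribution of the per-patient values.*

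**Before any data review**, do one of two things:
1. Name a target for retention and one for compliance (for compliance, for example, the share of patients who reach a stated level), and apply the same rule to both: feasible if the 95% interval lies above the target, not feasible if it lies below, otherwise inconclusive. For an illustrative 60% target with 40 patients, that is 31 or more, 17 or fewer, and 18 to 30. The investigators must choose and justify the targets.
2. Keep the analysis descriptive and change the verbs in the Abstract (Aims) and the Conclusion to *estimate* the feasibility of the programme.

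Under either option, support N = 40 with the precision it gives, about 13 to 16 points either side for observed rates of 50% to 80%. Verdicts by diagnosis should not be promised.

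**Cost:** wording in the protocol and analysis plan; no extra patients or measurements. The downside is that the conclusion may be less favourable, or openly inconclusive.
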